### Outcomes

#### Primary endpoint

Change in waist circumference was selected as the primary endpoint because of its validity as a superior measurement for assessing abdominal fat content and associated obesity health risk, as compared to a measure such as body mass index (BMI) [24–26]. In addition, there are existing national Malaysian data on population waist circumference, which allow for the study results to be comparable on a national level. In the present trial, the primary endpoint is predicted to provide a 2-cm reduction of waist circumference in the intervention group compared to the control group, which will reflect a reduction of central fat distribution. The reduction of 2 cm in waist circumference as a primary endpoint is based on the mean from a number of studies indicating that a decrement of waist circumference is possible with a lifestyle changing intervention over a period of 8 months [27–31]. The variation between the two time-points in these studies was small (standard deviation (SD) of 3–5) after the intervention period, and we therefore assume an expected within-person estimate of SD = 5.

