#### Sample size calculation

The sample size calculation is based on a 2-cm reduction in waist circumference, in the primary endpoint of waist circumference between the intervention and control arms at 8 months. Assuming a 5 % level of significance (alpha = 0.05), a statistical power of 90 % (beta = 0.10) and a SD of 5 cm using a two-sided *t* test, 132 women per arm are required. Taking into consideration a 20 % drop-out rate, and that 20 % will be pregnant, a total of 660 women would be randomised/enrolled to ensure 264 subjects to cover both the intervention and control arms.

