#### Randomisation

At the baseline measurement visit, subjects will be randomised into the intervention and control arms at a 1:1 allocation ratio. Random allocation sequences will be computer- generated with block sizes of six subjects. Each clinic will be provided with a sufficient number of identification (ID) numbers with randomisation codes. When a subject is enrolled in the trial, the study nurse should assign the lowest available ID number to the subject from the list of ID numbers.

The Institute for Health System Research (IHSR) under the MoH has prepared the randomisation list and these are distributed to the five designated primary health clinics in Seremban. A copy is maintained by the IHSR.

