#### Statistical analysis

The null hypothesis is that there is no difference in the change in waist circumference between the intervention and the control group after the 8-month intervention. The alternative hypothesis is that the decrement in waist circumference will be bigger in the intervention group compared to the control group after the 8-month intervention. A linear regression model will be used to assess the difference in the change of waist circumference from baseline to end of intervention, with the difference in waist circumference as the independent variable, treatment (intervention versus control) and baseline waist circumference as covariates. Additional tests will be performed for the impact of the intervention in both high- (waist circumference above 80 cm) and low-risk (waist circumference below 80 cm) groups. This will be done by subgroup analysis or by assessing the proportional changes in the primary endpoint. Each subgroup will also be analysed in a linear regression model. The continuous secondary endpoints will be analysed in a linear regression model, whereas the difference in the change of each secondary endpoint from baseline to end of intervention, will be the dependent variable, treatment (intervention versus control) and baseline value as covariate. Regarding health literacy (HL-EU-Q47), physical activity (IPAQ) and stress (DASS-21) all the variables are ordinal and, therefore, independence between intervention and control groups will be tested with the chi-squared test. Change in nutrient intakes will be compared between the groups using a generalised linear model, with additional adjustments for total energy intake. Nutrient and food patterns before and after the intervention will be explored in both groups separately by using dimension reduction techniques such as principal component analysis. Multivariate analysis will be performed to assess the association between exposure to the intervention, primary endpoints and secondary endpoints (BMI, waist-to-height and waist-to-hip ratio, HbA_1c_, lipid profile, blood pressure, health literacy, physical activity, dietary intake and stress level) using linear regressions. In this model the secondary endpoint will be included in the model as covariates and the estimated coefficients will be presented unadjusted and adjusted for appropriate and/or effect modifier and/or confounders. Furthermore, interactions between the secondary endpoints will also be explored. Several supportive analyses will be performed. The first supportive analysis will explore the relation between subjects’ and spouses’ change in waist circumference and other anthropometric measurements, diet, physical activity, health literacy and stress. A second supportive analysis will explore whether a short intervention period (subjects who become pregnant between 4.1 and 8 months in the intervention period), will also have an impact on the primary endpoint and secondary endpoints. A time variable explaining how long they have been included in the intervention will be included in the models as a covariate. At the end of the 12-month post-intervention monitoring period, a full analysis will be conducted on subjects who become pregnant within 12 months after completing the intervention. This will be done by assessing the incidences of GDM among women who became pregnant between treatment groups, using a chi-squared test. Additionally, a logistic regression model to explore associations between the number of subjects with GDM and several secondary endpoints will be conducted.

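### The subgroup tests above and below 80 cm cannot show whether the effect differs by baseline waist; an interaction term is needed for that

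*Protocol article*

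**What the plan says.** The Statistical analysis section of the protocol article first sets out the primary model: change in waist circumference regressed on treatment and baseline waist. It then announces additional tests of the intervention's impact in a high-risk group (waist above 80 cm) and a low-risk group (below 80 cm). On method it says "This will be done by subgroup analysis or by assessing the proportional changes in the primary endpoint", and then "Each subgroup will also be analysed in a linear regression model".

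The only interactions the section names are those between secondary endpoints. Effect modifiers are mentioned once, as possible adjustments in the multivariate model that has secondary endpoints as covariates. No term for treatment by baseline waist, continuous or dichotomised, appears anywhere, and the article does not say how the two subgroup results are to be compared.

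**The concern.** Two separate regressions test two separate null hypotheses, one of no effect in women above 80 cm and one of no effect in women below it. Whether the intervention works differently in the two groups is a third hypothesis, and neither regression tests it. With no other comparison named, the material a reader will have is a pair of p-values. Each subgroup holds only part of a sample sized for the whole trial, so the two p-values can easily fall on opposite sides of 0.05 when the effect is the same in everyone.

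At stake is any statement that the intervention suits high-risk women more than low-risk women, or the reverse. The groups carry those labels, so the contrast is a natural one for readers to draw. The primary comparison is not at stake.

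**Working it through.** **Inputs from the protocol article**
- Sample size calculation: a 2 cm between-arm difference ("The sample size calculation is based on a 2-cm reduction in waist circumference"); "level of significance (alpha = 0.05"; two-sided t test; SD 5 cm; 90% power; "132 women per arm are required".
- Primary endpoint: cited studies gave SDs of 3–5, and "we therefore assume an expected within-person estimate of SD = 5".
- Randomisation: "subjects will be randomised into the intervention and control arms at a 1:1 allocation ratio".

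**Assumptions.** The share of women on each side of 80 cm is not given, so I use 50:50 and 30:70. The true effect is 2 cm in both subgroups. Arms are equal within each subgroup.

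**Step 1: the plan's own figure.** n per arm = 2 × SD² × (1.960 + 1.282)² / difference² = 2 × 25 × 10.51 / 4 = 131.3, rounded up to 132. This matches the protocol.

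**Step 2: power within each subgroup.** With m women per arm, the standard error is SD × √(2/m), and power follows from the noncentral t distribution with noncentrality 2 / SE.
- 50:50: m = 66 in each subgroup. SE = 5 × √(2/66) = 0.870, noncentrality 2.30, power 62.6%.
- 30:70: m = 39.6 and 92.4. SE = 1.124 and 0.736, noncentrality 1.78 and 2.72, power 42.0% and 77.2%.

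**Step 3: exactly one subgroup significant.** The subgroups contain different women, so P = a(1 − b) + b(1 − a), where a and b are the two powers.
- 50:50: 2 × 0.626 × 0.374 = 46.8%.
- 30:70: 0.420 × 0.228 + 0.772 × 0.580 = 54.3%.

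**Step 4: sensitivity.** Losses of 20% to drop-out and 20% to pregnancy, applied to the 660 women randomised, leave 660 × 0.60 = 396. The SD is varied over the 3–5 range that the protocol reports.

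| Evaluable women | SD (cm) | 50:50 | 30:70 |
|---|---|---|---|
| 264 | 5 | 46.8% | 54.3% |
| 264 | 4 | 30.3% | 42.1% |
| 264 | 3 | 6.3% | 17.0% |
| 396 | 5 | 32.0% | 43.4% |
| 396 | 4 | 11.6% | 23.7% |
| 396 | 3 | 0.7% | 5.0% |

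Rounding the smaller subgroup down to whole women (39 or 59 per arm) moves the 30:70 figures at SD 5 to 54.7% and 43.6%.

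**Step 5: the interaction test.** Under a uniform effect, a two-sided 0.05 interaction test signals a difference in 5% of trials whatever the split or SD. Its power with 264 women and SD 5 uses SE = 5 × √(2/m₁ + 2/m₂), which is 1.231 (50:50) or 1.343 (30:70). For a 2 cm difference in effect between subgroups, power is 37% or 32%. For a 4 cm difference it is 90% or 85%. These figures are for the two-group interaction. Power for a continuous interaction depends on the waist distribution, which the article does not give.

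**The case against.** The strongest reply is that no comparison between the subgroups is planned. The article speaks of the impact within each group, lists the subgroups in neither the objectives nor the secondary endpoints, and nowhere says that differing significance will be taken as a differential effect. That is correct, so the percentages above are conditional on someone reading the results that way. A reader might infer that the trial will report a false subgroup difference about half the time; the text does not support that.

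The headline range also depends on its inputs. It takes the top of the reported SD range and exactly 264 evaluable women. At SD 3 the pattern arises in only about 1–17% of trials across the two sample sizes, and adjustment for baseline waist could bring the residual SD below 5. This stands, and the range has to be reported with the figure.

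A third reply is that the article condenses a fuller protocol, so an interaction term may be specified elsewhere. This carries less weight. The article does state a method, a separate regression per subgroup, and it does say which interactions will be explored. The relevant one is not among them.

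Two further readings go too far:
- The word joining subgroup analysis to proportional changes might suggest that the whole method stays open until data are seen. The following sentence has the subgroup regressions done in addition, so they are fixed either way. Proportional change is undefined and might be one way of asking whether the effect scales with waist. Dropping it is a matter of preference.
- The Discussion's argument for widening the focus beyond high-risk groups might suggest that these subgroups are meant to settle that question. The Discussion does not mention the 80 cm groups.

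**Conclusion.** The point holds as a limit on what the planned analysis can show: separate tests above and below 80 cm give no valid basis for saying that the effect differs between them. If significance in one group only were read as a difference, the error rate under a uniform 2 cm effect would be about 47–54% at the design values and about 32–43% with 396 women. It falls steeply with a smaller SD, and at SD 3 with 396 women it is no higher than the interaction test's 5%. All these figures rest on an assumed split at 80 cm and on the same true effect in both groups. The analysis is additional and the primary test is untouched, so this is a worthwhile correction to the plan and not a threat to the trial's main conclusion.

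**What to change.** - Alongside the primary analysis, fit one model in all women: waist change on treatment, baseline waist (continuous) and their interaction. Base any claim of a differential effect on the interaction estimate and its 95% CI.
- Present the effects below 80 cm and at 80 cm or more as descriptive estimates with CIs. The continuous-interaction model does not give these directly. Take them from a companion model with a treatment-by-subgroup term, or report model-predicted effects at stated waist values. Wording the cut as below 80 versus 80 or more also places women at exactly 80 cm, whom the current wording leaves in neither group.
- State in advance that the interaction test has low power (about 32–37% for a 2 cm difference in effect at 264 women, two-group version), so a non-significant interaction does not show equal effects.
- If the proportional-change analysis is kept, define it and say what question it answers.

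The cost is a few lines in the analysis plan and one or two extra model terms. No new data, visits or participants are needed.

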**Method/design:**

Eligible subjects will be Malaysian women in the age group 20 to 39 years, who are nulliparous, not diagnosed with diabetes and own a smartphone. With an alpha-value of 0.05, a statistical power of 90 %, 264 subjects will need to complete the study. Subjects with their spouses will be randomised to either the intervention or the control arm for an 8-month period. The primary endpoint is change in waist circumference from baseline to end of intervention period and secondary endpoints are changes in anthropometric parameters, biochemical parameters, change in health literacy level, dietary habits, physical activity and stress level. Primary endpoint and the continuous secondary endpoints will be analysed in a linear regression model, whereas secondary endpoints on an ordinal scale will be analysed by using the chi-squared test. A multivariate linear model for the primary endpoint will be undertaken to account for potential confounders. This study has been approved by the Medical Research and Ethics Committee of the Ministry of Health Malaysia (protocol number: NMRR-14-904-21963) on 21 September 2015.

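### Health literacy, physical activity and stress are tested with a chi-squared test that ignores category order and baseline; it is valid under randomisation but inefficient and not directed at improvement

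*Protocol article*

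**What the plan says.** The Secondary endpoints section defines health literacy (the European 47-item questionnaire), physical activity and sedentary behaviour (IPAQ) and stress (DASS-21) each as a change between baseline and 8 months.

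The Statistical analysis section then says of the three measures that "all the variables are ordinal and, therefore, independence between intervention and control groups will be tested with the chi-squared test". The Abstract gives the same rule: "secondary endpoints on an ordinal scale will be analysed by using the chi-squared test". Neither place names a trend version, a covariate, or whether the table is built from 8-month categories or from categories of change.

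In the same paragraph the continuous secondary endpoints are handled differently. Their change "will be the dependent variable, treatment (intervention versus control) and baseline value as covariate".

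The only sample size stated is for the primary endpoint: "132 women per arm are required". No power is claimed for the three ordinal measures.

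**The concern.** The reason given points the wrong way. Pearson's test of independence gives the same result however the categories are shuffled, so it discards the very property cited to justify it. A shift of the whole distribution towards better categories, which is what the intervention aims at, is spread over several degrees of freedom instead of one.

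The baseline category is also left out. For endpoints defined as change, baseline is usually the strongest available predictor, and the protocol already uses it for the continuous endpoints.

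The Aim section lists health literacy, physical activity, sedentary behaviour and stress among the secondary objectives, and the chi-squared test is the only between-arm test stated for them. At stake is a missed behavioural effect, or a significant result that cannot be read as better or worse.

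**Working it through.** **Inputs from the protocol (Sample size calculation).** A difference of 2 cm ("The sample size calculation is based on a 2-cm reduction in waist circumference"), SD 5 cm, two-sided alpha 0.05, power 90%, 132 women per arm.

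**Reproducing the plan's figure.** n per arm = 2(1.960 + 1.282)² × 5² / 2² = 131.3, rounded up to 132. The power at 132 is 90.1% by the normal approximation and 89.9% by the noncentral t. The stated number is right, and 132 per arm is used below.

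**Assumptions, not in the protocol.** A normal latent variable shifted by 0.3 or 0.4 SD (0.4 = 2/5, borrowed from the primary endpoint); three to five categories; baseline to 8-month correlation of 0.3 to 0.7.

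**Step 1: cost of ignoring order.** With category proportions p0 and p1 in the two arms and pooled p̄, Pearson's test has noncentrality λ = (n/2) Σ (p1 − p0)² / p̄ on k − 1 df. An ordered (Wilcoxon-type) test has 1 df.

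Example: three equal control categories and a shift of 0.4 SD.
- The cut-points are ±0.431, so the shifted arm has about 20.3 / 30.9 / 48.8%.
- Σ (p1 − p0)² / p̄ ≈ 0.123, so λ ≈ 66 × 0.123 ≈ 8.1.
- Power is 72.5% on 2 df (chi-squared) and 81.3% for the ordered test.

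The same calculation for other layouts (chi-squared to ordered):
- 0.4 SD: four categories about 70% to 84%; five equal 67% to 85%; five skewed 46–56% to 67–77%.
- 0.3 SD: three equal 47% to 58%; four about 44–45% to 61%; five equal 41% to 62%; five skewed 28–33% to 45–52%.

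Ignoring order alone costs about 9 to 21 points. As a general rule, the noncentrality that gives 90% on 1 df gives 83.5%, 78.4% or 74.0% on 2, 3 or 4 df.

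**Step 2: cost of ignoring order and baseline.** Simulation, 1,000 trials per setting, 132 per arm. The baseline-adjusted analysis is a linear model on category scores, standing in for an ordinal model. The three figures in that column are for correlations 0.3 / 0.5 / 0.7. Category proportions are 10/40/35/15% (four) and 70/12/10/5/3% (five).

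| Categories | Shift (SD) | Chi-squared | Ordered, no baseline | Ordered, with baseline | Loss (points) |
|---|---|---|---|---|---|
| 3 equal | 0.3 | 48–49% | 57–59% | 62 / 64 / 76% | 14–27 |
| 3 equal | 0.4 | 72–74% | 81–82% | 86 / 86 / 94% | 11–22 |
| 4 unequal | 0.3 | 44–46% | 59–61% | 64 / 71 / 83% | 20–37 |
| 4 unequal | 0.4 | 71–73% | 84–85% | 88 / 92 / 98% | 17–25 |
| 5 skewed | 0.3 | 30–34% | 50–52% | 52 / 57 / 67% | 20–37 |
| 5 skewed | 0.4 | 53–56% | 76% | 79 / 82 / 92% | 26–37 |

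The chi-squared test on 8-month categories does not use baseline, so its spread across correlations is simulation noise.

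**Step 3: the same with a fitted proportional-odds model.** Shift 0.3 SD, 300 trials per setting, correlations 0.3 / 0.5 / 0.7.
- Three equal categories: chi-squared 48 / 47 / 52%, proportional odds 60 / 62 / 77%.
- Five skewed categories: chi-squared 32 / 35 / 32%, proportional odds 55 / 62 / 75%.

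The gains run from 12 to 43 points, and each figure carries a Monte Carlo standard error of up to √(0.25/300) = 2.9 points. Together with Step 2, a fair summary is roughly 10 to 40 points.

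**Step 4: rejection without benefit.** Take 30/40/30% against 20/60/20%, two distributions with the same average position. Σ (p1 − p0)² / p̄ = 0.01/0.25 + 0.04/0.50 + 0.01/0.25 = 0.16, so λ = 66 × 0.16 = 10.56, and the chi-squared test rejects about 84% of the time.

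**Step 5: if change categories are tabulated instead.** Chi-squared on worse / same / better had simulated power of 29% to 86% over the Step 2 settings. In every setting this was below the baseline-adjusted analysis.

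**The case against.** The strongest case against is that nothing here is invalid. Under 1:1 randomisation the chi-squared comparison keeps its type I error, these are secondary endpoints with no claimed power, and the primary analysis is untouched. All of that stands.

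The size of the loss is also not a property of the documents. Shift, number of categories, skew and correlation are assumed. With three balanced categories and low correlation the loss is only about 10 to 12 points, so a general statement that most of the power is lost would not be supported.

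Two stronger readings are tempting.

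- A reader might infer that the test does not address change at all. The protocol does not settle this, because it does not say what is tabulated. With 8-month categories the test compares final status, which is a valid randomised comparison. With worse / same / better it does address change, though still without order. A condensed article may leave that detail to the full protocol.
- A reader might infer that the later multivariate linear regressions contradict the ordinal rationale. They do not. Those models enter the secondary endpoints as covariates, and an ordinal predictor in a linear model is no contradiction. For the same reason they supply no alternative between-arm test of these three measures.

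The full protocol or analysis plan may also specify effect estimates and intervals, so their absence from the article is not counted as a fault. What the objection does not remove is that the article fixes a method and gives a reason for it, and the reason argues for a different method.

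**Conclusion.** The point holds as one of efficiency and direction. The protocol chooses an unordered, unadjusted test because the measures are ordinal, for endpoints it defines as changes, beside continuous endpoints that it does adjust for baseline. At 132 per arm, with latent shifts of 0.3 to 0.4 SD, three to five categories and correlations of 0.3 to 0.7, the loss against a baseline-adjusted ordinal analysis is roughly 10 to 40 percentage points. Ignoring order accounts for about 9 to 21 of these. The adjusted analysis had more power in every setting tried. Confidence is high in the defect of method and moderate in its size, which depends wholly on those assumptions. The change should be made, but no primary conclusion depends on it.

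**What to change.** For each of the three measures, make the between-arm test a proportional-odds model of the 8-month category with treatment and baseline category as covariates, and report the odds ratio with its 95% CI. State that this model decides. Keep the chi-squared tables as description only. Where a total score exists (the Safety monitoring section refers to a score for DASS-21), use the baseline-adjusted linear model already planned for continuous secondary endpoints as a supportive analysis. Bring the sentence in the Abstract into line.

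The cost is wording and a standard ordinal regression command in the named software. No new data are needed, since the Data collection section has all three questionnaires completed at baseline and at the endpoint visit. The small downside is that the proportional-odds assumption has to be checked.

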#### Supportive data

Anthropometric measurements, blood pressure and data on physical activity, dietary, stress and health literacy will be collected from the subject’s spouse. Socio-demographic data and family medical history will be collected from both the subject and the spouse. These variables are collected to adjust for confounding effects.

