#### Data collection

At baseline the subjects will undergo measurements of waist circumference, hip circumference, weight, height and blood pressure by following standardised procedures based on World Health Organisation (WHO) STEPS surveillance [32]. Only the subject in the couple will provide a 10-mL blood sample to measure glycated haemoglobin A_1c_ (HbA_1c_) and a fasting lipid profile (triglycerides (TG), low-density lipoprotein cholesterol (LDL-C), high-density lipoprotein cholesterol (HDL-C) and total cholesterol (TC)). Due to the need for a fasting lipid profile analysis, the subject will be asked to come to the clinic after fasting for a minimum of 9 h. In line with this, the data collection time-points are planned to be in the morning. The European Health Literacy Tool Q-47 (HL-EU-Q47) [33] (HL-EU Consortium 2012), the Malaysian Food Frequency Questionnaire (FFQ), modified to be used in the current trial [2]; the International Physical Activity Questionnaire (IPAQ) [2]; and the Depression Anxiety Stress Scale 21-items (DASS-21) [34, 35] will be used to collect data on level of health literacy, dietary pattern, physical activity level, and stress level, respectively. Data such as socio-demographic parameters and family history of diabetes will be collected by structured interviews with the study nurse. The spouse will undergo the same data measurements, with the exception of blood sampling. At the end of the data collection, and before subject and spouse leave, data will be checked by the study nurse and site coordinator or research officer, to ensure that all data forms and questionnaires have been filled correctly. When data collection is completed the data collection forms and questionnaires will be signed-off by the study nurse and site coordinator or research officer. At the end of the baseline visit, if the subject is randomised to the intervention, the first contact with a CHP will be made. The subject and spouse will be introduced to the mobile application and it will be installed on the subject’s and spouse’s smartphone device. If the subject and spouse have sufficient time the CHP will proceed with the first contact point. If the subject and spouse do not have the time, an appointment will be set in the next 5 days either at the clinic or at the couple’s house. The same measurements, except height, socio-demographic parameters and medical history, described above will be conducted at the endpoint visit (Table 2).

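### The additional multivariate model takes secondary endpoints, defined as eight-month changes, as covariates; one of them restates waist change, so its treatment coefficient is not an adjusted intervention effect

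*Protocol article*

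**What the plan says.** The Statistical analysis section of the Protocol article describes two different models for waist circumference.

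- **Main model.** Change in waist is regressed on "treatment (intervention versus control) and baseline waist circumference as covariates". This model addresses the null hypothesis.
- **Additional model.** "Multivariate analysis will be performed to assess the association between exposure to the intervention, primary endpoints and secondary endpoints" by linear regression. The listed secondary endpoints begin with "BMI, waist-to-height and waist-to-hip ratio" and go on to HbA1c, lipids, blood pressure, health literacy, physical activity, diet and stress. The section then says: "In this model the secondary endpoint will be included in the model as covariates". Coefficients are to be shown with and without adjustment.

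The Abstract (Method/design) says: "A multivariate linear model for the primary endpoint will be undertaken to account for potential confounders". This appears to be the same additional model.

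Two other sections settle what the covariates are. Secondary endpoints defines each one as a change from baseline to eight months. Data collection says: "The same measurements, except height, socio-demographic parameters and medical history, described above will be conducted at the endpoint visit".

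**The concern.** A variable measured after randomisation, which the intervention is designed to move, cannot confound the comparison of the randomised arms. It is a mediator, a parallel outcome or, for the waist ratios, partly the outcome itself. Once it is in the model, the treatment coefficient no longer estimates the effect of the intervention on waist. It estimates what is left after holding fixed the things the intervention may have changed.

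The risk is one of interpretation. A real 2 cm effect from the main model could stand in the report beside an adjusted estimate near zero. With the Abstract's wording attached, a reader could take the effect to be explained by confounding. This is not a detail left open for an analysis plan, because the article names the covariates.

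**Working it through.** **Inputs from the Protocol article.** Effect 2 cm, SD 5 cm, two-sided 5 % level, 90 % power and 132 per arm (Sample size calculation); 1:1 allocation (Randomisation); secondary endpoints defined as changes (Secondary endpoints); no height at the endpoint visit (Data collection).

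**1. The plan's own figure.** n per arm = 2 × (1.9600 + 1.2816)² × 5² / 2² = 131.3, rounded up to 132. Power at 132 is 0.901. The noncentral t version gives 133 per arm and power 0.899 at 132, an immaterial difference. The figure reproduces.

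**2. Waist-to-height ratio.** Let W0 and W1 be waist at baseline and eight months, and h the single height measurement. Change in ratio = W1/h − W0/h = (W1 − W0)/h, so waist change = h × change in ratio. If all women had the same height, the covariate would determine the outcome exactly and leave nothing for treatment. Heights differ, so the identity across women is slightly loose. With an assumed mean of 156 cm and SD of 4 to 7 cm, the coefficient of variation is only 4/156 = 2.6 % to 7/156 = 4.5 %.

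**3. BMI.** Let r be the within-arm correlation of BMI change with waist change. Let f be the standardised treatment effect on BMI change as a fraction of that on waist change (2/5 = 0.4 SD). The expected treatment coefficient after adding BMI change is −2 × (1 − r × f):
- r = 0.5, f = 1: −1.0 cm
- r = 0.7, f = 1: −0.6 cm
- r = 0.3, f = 0.5: −1.7 cm

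**4. Simulation.** 264 completers, true effect −2 cm, SD 5 cm, 1,000 replicates per scenario. Every model contains treatment and baseline waist. Assumptions not in the documents:
- baseline waist mean 78 cm, SD 11 cm
- height mean 156 cm
- BMI change SD 1.2 kg/m²
- baseline hip mean 95 cm, with slope 0.6 on baseline waist and residual SD 8 cm
- hip change = 0.6 × k × waist change, plus noise of SD 3 cm

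Scenarios (height SD; r; f; k): A = 5.5; 0.5; 1; 0.5. B = 5.5; 0.7; 1; 0.5. C = 7; 0.7; 1; 0.5. D = 4; 0.3; 0.5; 0.3.

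Mean treatment coefficient in cm (rejection rate):

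| Model | A | B | C | D |
|---|---|---|---|---|
| Main model | −1.991 (0.889) | −1.972 (0.888) | −2.005 (0.917) | −2.002 (0.897) |
| + baseline waist-to-height and waist-to-hip | −1.994 (0.891) | −1.974 (0.892) | −2.006 (0.914) | −2.000 (0.890) |
| + change in waist-to-height | −0.003 (0.041) | −0.002 (0.059) | −0.005 (0.053) | −0.002 (0.030) |
| + 8-month waist-to-height | −0.455 (0.325) | −0.470 (0.350) | −0.668 (0.463) | −0.287 (0.240) |
| + change in BMI | −1.003 (0.445) | −0.571 (0.248) | −0.602 (0.264) | −1.702 (0.819) |
| + change in waist-to-hip | −0.617 (0.417) | −0.621 (0.421) | −0.636 (0.438) | −0.516 (0.373) |
| + all three changes | −0.002 (0.043) | −0.001 (0.052) | −0.003 (0.050) | −0.001 (0.028) |

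Baseline covariates leave the effect and the power intact. Change in waist-to-height ratio removes the effect in every scenario. The other rows attenuate it by amounts that depend on the assumptions.

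**The case against.** The strongest reply has three parts.

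- **Purpose.** The Statistical analysis section presents the model as a study of association and goes on to explore interactions between secondary endpoints. That is close to an exploratory analysis, and results with and without adjustment would make any attenuation visible. This is fair, and it lowers the severity. It does not make the treatment coefficient interpretable, and nothing in the section labels the model exploratory.
- **Time-point.** The model description does not say whether baseline, 8-month or change values enter. That is correct, and baseline values would cause no such bias. But the protocol defines a secondary endpoint only as a change, and where the same section means a baseline value it says so.
- **Confounders.** The documents never call the secondary endpoints confounders. The Abstract's phrase could refer to the socio-demographic, family-history and spouse data, of which Supportive data says: "These variables are collected to adjust for confounding effects". The link between the Abstract and this model is therefore an inference, though a reasonable one.

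A reader might infer more than the documents support:

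- **That the primary result is compromised.** It is not. The main model is separate and contains only treatment and baseline waist.
- **That the nutrient analysis has the same fault.** The plan says: "Change in nutrient intakes will be compared between the groups using a generalised linear model, with additional adjustments for total energy intake". It gives no time-point for energy intake. Energy-adjusted change also answers a different question, about the composition of the diet.
- **That spouse data measured at the endpoint will be used for adjustment.** No time-point is given for that use. Changes in spouses appear only in a supportive analysis of how they relate to changes in the women.
- **That adjustment is needless because the trial is randomised.** This is too absolute for completers after drop-out and withdrawal for pregnancy. Baseline adjustment remains legitimate.

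**Conclusion.** The point holds for the additional multivariate model only. As written, with secondary endpoints in the sense the protocol gives them, that model cannot yield an adjusted intervention effect.

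The near-zero coefficient with change in waist-to-height ratio follows from the definition of the ratio and the single height measurement. It held for every height SD tried. The attenuation with the 8-month ratio, BMI change or waist-to-hip change is real in direction under the scenarios examined, but its size rests on correlations and SDs assumed here. If baseline values were intended, the bias disappears and the wording alone is at fault.

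The passage should be corrected before analysis. It does not threaten the trial's main conclusion.

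**What to change.** - In any adjusted model of the treatment effect, use only covariates fixed before randomisation: baseline waist, baseline values of the other measures, age, ethnicity and clinic. State the time-point of each.
- Keep regressions of waist change on changes in the secondary endpoints as a separately labelled exploratory association or mediation analysis. Leave waist-to-height and waist-to-hip ratio out of it, and do not report its treatment coefficient as an adjusted intervention effect.
- Keep the Abstract's reference to confounders, but attach it only to the baseline-adjusted model.

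The cost is a change of wording. The women's baseline measurements are already collected, and neither the sample size nor the main analysis changes.
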